**Figure 1. Summary flow chart**

[figure not shown]

## Overview

***Cervical cancer is one of the few PREVENTABLE cancers. Screening can detect pre-cancer that can be treated, thereby preventing the development of a potentially fatal cancer.***

Cervical cancer is caused by high-risk types of Human Papillomavirus (HPV) and it is globally recognised that testing for the HPV virus, as a primary screen is more effective than cervical cytology (smear) in detecting cervical changes that may lead to cancer. Screening in Aotearoa New Zealand utilises the less effective cervical cytology (smear) as a primary screen. Switching to HPV primary testing has the potential to reduce incident cervical cancers by 15% annually compared to the present cytology programme.

Aotearoa has a National Cervical Screening Programme (NCSP) that was established in 1990 utilising a register and regular screening and recall systems centrally and through primary care. The current cervical screening programme has significant inequities. The government have recently announced

funding for a new cervical screening programme which will include the offer of HPV self-testing. However, this will not be rolled out until August 2023. Our study will answer important questions for the National Screening Unit (NSU) about how the new programme should be implemented including information on women who need further investigation after a positive HPV test. Important questions remain to be answered about the *universal offer of HPV self-testing* approach before an equitable, high quality national programme of HPV primary screening for cervical cancer prevention is implemented.

*This health delivery grant (Te Tai Tokerau project) will address these unanswered questions with the research team working in partnership with the Primary Health Entity (PHE) Mahitahi Hauora in Te Tai Tokerau/Northland region.*

The present national screening programme (cervical cytology) has been functioning for 30 years and it is crucial that changing to an HPV primary testing programme is fully informed and achieved without loss of coverage and follow up. If this is maintained with the more effective HPV test then the programme will prevent more cancers and save more lives than the present cytology program. Increasing coverage with the HPV self-test will potentially contribute to a more equitable program.

#### *Universal offer of HPV self-testing*

The *universal offer of HPV self-testing* approach means all eligible wāhine will be offered an HPV self-test as the primary screening test. If the wāhine declines the self-test, she will be offered the conventional cervical cytology screen.

We do not yet know the best models for implementation of a high quality effective HPV testing program utilising universal offer of HPV self-testing approach for all eligible women.

Before adopting *universal offer of HPV self-testing* as the primary approach for the NCSP it must be proven that it achieves coverage results that are non-inferior (at least equal) to the present programme. Screening coverage is the proportion of eligible women screened in the previous three years. A screen is defined as either an HPV self-test, clinician taken HPV test or cervical cytology. The MOH target is to reach 80 percent screening coverage for all eligible women, including separately for women in Māori, Pacific, Asian and European/Other population groups.

In addition, triage and referral to colposcopy after a positive high risk HPV test needs to be trialled to ensure these pathways are equitable.

#### **Evidence to date**

Our recent research (He Hapu Te Whare Tangata Randomised Controlled Trial (RCT), HRC17-193) has shown that the offer of an **HPV self-test** (without speculum exam) is successful in reaching under-screened or never-screened Māori women compared to the current offer of a routine cervical smear. This project was delivered at the general practice level and any model scale up would need to be implemented through primary care organisations (PHOs) or their equivalent after the health and disability system reforms.

#### **Why choose Te Tai Tokerau/Northland region for this project**

Any proposed equitable cervical screening programme must be effective across a diverse population but it must also extend to those women that the programme has been failing to reach, particularly Māori and those in rural areas. Therefore, our model is based on implementation through primary care organisations (PHOs). Primary health organisations (PHOs) ensure the provision of essential primary health care services, mostly through general practices, to people who are enrolled with the PHO. PHOs are funded by district health boards (DHBs), who focus on the health of their population.

There are approximately 30 PHOs in New Zealand and they care for almost all New Zealanders. Mahitahi Primary Health Entity is Northland's PHO formed through consolidation of the prior rural and urban PHOs. Te Tai Tokerau/Northland has a high Māori population and is a diverse rural/urban area. Our successful RCT (He Tapu Te Whare Tangata) offering HPV self-testing to under screened, primarily Māori and rural women was undertaken in Northland general practices. Hence, we have strong existing networks within this community, primary care and with the Northland DHB.

Our partnership, working with the Ministry of Health, will inform the NSU how to best implement a high quality, equitable, efficient and sustainable primary HPV screening programme. The ultimate goal is **to reduce cervical cancer incidence and death for Māori and non-Māori in Aotearoa NZ.**

**COVID 19:** Please note that since the COVID 19 emergency, screening rates have decreased sharply and the need for clarification of quality issues and implementation around the offer of universal HPV self-testing approach is even more urgent as this is a realistic alternative to the present system which involves an "in person" contact with an intrusive genital examination at a specified facility.

## **Background**

### **The New Zealand National Cervical Screening Programme (NCSP)**

The NCSP was established in 1990 to reduce the number of women who develop cervical cancer and those who die from it. Through routine screening at regular intervals, the programme aims to detect precancerous squamous cell changes, which, if not treated, may lead to cancer. Since the introduction of the NCSP in 1990 the age-standardised incidence rate of invasive cervical cancer has fallen by approximately 50% but Māori rates remain higher than those for non-Māori. Approximately 160 women are diagnosed with cervical cancer every year and 60 die from this largely preventable disease, despite the availability of an organised screening programme. About half the women who develop or die from cervical cancer have never been screened, and about a third have only been screened irregularly and infrequently.

### **Cervical Cancer Inequities and the National Cervical Screening Programme in Aotearoa/New Zealand**

Māori are more than twice as likely to be diagnosed with cervical cancer and almost three times more likely to die of cervical cancer than Pākehā. These cancers are preventable and disproportionately affect young Māori women. It is the second leading cause of cancer mortality for Māori women aged 25-44.

**In Aotearoa (NZ) the NCSP is failing Māori women, with 35% unscreened compared to 20% of N.Z European women unscreened and these disparities have increased due to COVID.**

Cervical cancer detection programmes require high levels of screening to be successful in bringing down cancer rates. The majority of cervical cancers occur in women who have either **not received screening or have had access to less frequent screens.** The present cervical screening program involves a speculum exam and taking a cervical sample for cytology. Pre-cancerous cells - representing cervical intraepithelial neoplasia (CIN) - may be detected, with more abnormal cells being associated with more advanced pre-cancerous disease (often abbreviated to CIN2 or CIN3). Cytological examination may also detect carcinoma in situ or invasive cervical cancer. Abnormal results trigger a variety of follow-up pathways, which may involve colposcopic examination (microscopic examination by a gynaecologist) and biopsy.

Taking cervical samples for cytology is an invasive procedure that requires attending a clinic and has associated transport/costs. For Māori women, these are barriers to screening including having to attend a clinic, access issues due to rurality, cost, challenges with transport or time off work, fear of results, and the pain, embarrassment, (whakamā) or discomfort of a genital examination.

### **HPV self-testing potentially overcomes access issues for Māori and for other under-screened groups.**

This project recognises that equity is for all groups. We acknowledge that it covers all peoples with cervixes including trans and non-binary peoples who are underserved by the health system and will also benefit from HPV self-testing. In this study the term women is used as a surrogate for people with cervixes. Hence, this proposed study examining the *universal offer of HPV self-testing* approach is important for any proposed equitable quality programme to prevent cervical cancer.

### **Human Papillomavirus (HPV)**

HPV is the causative agent of cervical cancer. Infection with certain high risk oncogenic (cancer forming) types of the HPV cause the changes in the cells of the cervix that can lead to cancer. In this protocol HPV refers to these high-risk oncogenic types. While infection with HPV is common, most infections are transient and spontaneously clear without clinical consequences. However, some women develop persistent HPV infections and are at risk for cervical cancer and its precursors. HPV types 16 and 18 are responsible for 70% of cervical cancers and a group of types, (usually abbreviated to 'other') account for a much smaller percentage of cancers. The knowledge about the cause of cervical cancer coupled with rapidly developing innovative preventive (vaccine) and detection (HPV testing) technologies now creates the potential to substantially reduce and eliminate the incidence of cervical cancer as called for by the World Health Organisation (WHO).

The majority of New Zealand women of screening age will not be vaccinated at this stage. All women vaccinated or not, need to be involved in a cervical screening programme as the vaccine does not cover all HPV types responsible for cervical cancers.

### **Primary HPV-based screening**

HPV testing is life-saving technology. This new Evidenced Based Practice (EBP) is more effective both in detecting pre-cancer changes on the cervix, and in preventing cervical cancer than cytology. A large body of evidence, including data from randomised trials in high and middle-income countries, has shown HPV testing as primary screening is superior to cytology in reducing cervical cancer incidence and mortality. The long term follow up of 24,510 women in the ARTISTIC RCT has now been completed and showed a similar level of protection 10 years after a negative HPV test compared with three years after a negative cytology test. Analysis of four European randomised controlled trials found that, compared with cytology, HPV-based screening provided 60–70% greater protection against developing invasive cervical cancers.

HPV testing in cervical screening detects high-grade lesions earlier than cytology, thus preventing more invasive cervical cancers. In addition, a negative HPV test provides greater reassurance of low pre-cancer risk than a negative cytology result and means that screening intervals can be increased to 5 years instead of the current 3 years. The Netherlands, Australia and UK have moved to HPV testing as the primary test using cervical/speculum sample in 2017, 2017 and 2019 respectively. HPV testing is projected to decrease cervical cancer incidence in Australia by 15–18% and cancer mortality by 16–18%, compared with current cervical smear practice.

### **HPV self-test**

[figure not shown]

The HPV self-test, a vaginal swab, can be used for HPV screening, providing sensitivity and specificity comparable with clinician-collected specimens. The test available in Aotearoa/NZ differentiates between types 16, 18 and a group of ‘other’ high risk types.  A no speculum, HPV self-test, has great potential to reduce disparities in screening since women are able to do the test themselves in a variety of settings including clinics, community centres and their homes. This eliminates a number of barriers for Māori women, and increases the potential to reduce disparities in detection of cervical abnormalities so reducing cervical cancer. If access to the more effective innovative HPV primary testing is limited by barriers such as using the intrusive cervical/speculum sample, then there is the potential to further increase cervical cancer disparities.

### **HPV self-test is acceptable and effective**

International and national studies including our recent randomised controlled trial (RCT) in Northland, suggest that HPV self-testing is acceptable and effective.

The ‘IMPROVE’ non-inferiority trial was carried out to compare self-testing with clinician-collected testing and showed a similar accuracy of detection for high grade pre-cancer between the two groups validating this approach.

Our He Tapu Te Whare Tangata randomised controlled trial (RCT) offered HPV self-testing to under screened women. It successfully engaged under or never screened Māori women in both testing and follow-ups. These women had either never had a smear or not had one for more than 4 years. Results show that the offer of HPV self-test reached over 50% of under-screened Māori women compared to 21% of the control (that is women who were offered a smear). In women who had never screened, the offer of self-test reached over 40% of women compared to just 12% of never screened in the control group. More than 80% of women took their own swab and a significant number (around 20%) took the self –test in their own home. The importance of multiple access points for taking the swab and the effect of community outreach were identified as vital to the success of the study.

The results of the RCT provide a strong argument for resources to be directed to general practices to carry out this project.

### **Proposed new national cervical screening programme and the Te Tai Tokerau project**

At the time of designing this study the New Zealand Ministry of Health (MOH) planned to shift the cervical screening programme to primary HPV testing in the future and as we were developing the study protocol the government announced funding for a new cervical screening programme which will include the offer of HPV testing. This shift will happen in 2023. The MOH has formed an HPV primary screening project group (the Technical Reference group) to advise the programme (PI [name] is a member). As Aotearoa New Zealand adopts the *universal offer of HPV self-testing* approach, we will be the first programme in high-income countries offering self-testing as the main test. This *universal offer of HPV self-test* has the potential for significant national and international impact.

This **Te Tai Tokerau project** will inform the MOH as to the non-inferiority of the *universal offer of HPV self-testing* approach. This is necessary before any such programme can be implemented.

**The ultimate goal is the successful implementation of an effective, sustainable, and equitable cervical screening programme.**

## **Methodology**

## **Aim**

The primary aim of this Te Tai Tokerau project is to test whether the cervical screening coverage utilising the *universal offer of HPV self-test programme* approach is non-inferior to the cervical screening coverage in the current cytology cervical screening programme.

We hypothesise that

The *universal offer of HPV self-testing* approach leads to the same or more numbers of women having a cervical screen compared to usual cervical cytology screening (includes all women due a screen, under-screened and never-screened women).

The *universal offer of HPV self-testing* programme approach is where the HPV self-test is the screen offered to all women due a cervical screen. Women can have cervical cytology as an alternative screen if they prefer this option, although the HPV self-test will be the preferred pathway in this approach.

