## **Data analysis**

**Primary outcome analysis:** comparing the screening coverage of two approaches.

1. Universal offer of HPV self-test approach
2. Offer of cervical cytology as per current approach

The two approaches will be compared using a Linear Mixed Model with a logit link, with practice fitted as a random effect. Non-inferiority for the primary outcome will be evaluated by observing whether the lower bound of the two-sided 95% confidence intervals for the difference in screening coverage between the two arms is above the non-inferiority limit of -10. If non-inferiority is evident, assessment as to whether the implementation has effectiveness superior to that of standard care will be carried out using the same approach but comparing to a zero difference. The primary analyses will be carried out on an intention-to-treat (ITT) basis. Per-protocol sensitivity analyses will also be conducted excluding participants who had major protocol violations. To account for any potential imbalance in underlying risk factors for screening uptake, sensitivity analyses will adjust for age, ethnicity, deprivation index, screening history and primary care practice.

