### Sample size

The NSCP coverage report from December 2019 for the Northland DHB shows that approximately 72.5% of women (33,403/46,090) aged 25-69 were screened over a period of 3 years. A total of fourteen practices and 5600 women (seven practices offering HPV-self-testing universally over a one-year period to approximately 2800 women, and seven practices providing routine clinical care

 HDEC amendment approved December 2021

data for approximately 2800 women about cervical cytology uptake) will give 95% power at a one-sided significance level of 2.5% to detect a non-inferiority margin of 10% between the two groups (i.e. the screening rates at participating practices will be no worse than 10% less than the screening rate obtained from the comparative data). This margin of error was chosen as we believe it is the smallest value that is clinically relevant. For this sample size we assumed a screening rate of 72.5% in the comparative data and 72.5% in the participating practices, and an average practice size of 400 participants and intra-cluster correlation coefficient of 0.01.

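### The aim and the condition for adoption speak of coverage no lower than now, but the primary rule only excludes a loss of 10 points or more

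*Protocol*

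**What the plan says.** Four places in the Protocol describe what the trial is to establish.

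- **Aim.** The primary aim is to test whether coverage under the new approach "is non-inferior to the cervical screening coverage in the current cytology cervical screening programme". No margin is given there. The hypothesis that follows is that the approach "leads to the same or more numbers of women having a cervical screen compared to usual cervical cytology screening".
- **Universal offer of HPV self-testing.** Before adoption, "it must be proven that it achieves coverage results that are non-inferior (at least equal) to the present programme".
- **Overview.** The change of programme should be "achieved without loss of coverage and follow up".
- **Proposed new national cervical screening programme and the Te Tai Tokerau project.** The trial will inform the Ministry on non-inferiority, and "This is necessary before any such programme can be implemented".

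Two places fix the rule.

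- **Data analysis.** Non-inferiority is shown if the lower bound of the two-sided 95% confidence interval for the difference "is above the non-inferiority limit of -10". If so, the same interval is then compared with zero to assess superiority.
- **Sample size.** The margin is 10%, explained as a screening rate at participating practices no more than 10% below the comparison rate. On its choice: "This margin of error was chosen as we believe it is the smallest value that is clinically relevant".

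**The concern.** The hypothesis and the adoption condition are statements about a difference of zero or more. The rule is a statement about a difference above -10 points. Tolerating a margin is normal in a non-inferiority trial. The difficulty is that the section on the universal offer itself explains non-inferior as at least equal, and treats that as the thing to be proven. A trial that meets its primary criterion will not have proven it. Since the result is meant to inform a decision on a national programme, the text should not invite a stronger conclusion than the test supports.

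The reason given for the margin adds to the difficulty. If 10 points is the smallest difference that matters clinically, every smaller loss is by implication unimportant. Yet the protocol works towards an 80% coverage target from which the region as a whole is less than 10 points away.

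**Working it through.** **Inputs** (Sample size section): 7 practices and about 2,800 women per group, 400 women per practice, intra-cluster correlation 0.01, coverage 72.5% in both groups, margin 10%, one-sided 2.5%, power 95%. I read the margin as 10 percentage points; step 2 supports that reading.

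**1. Precision**
- Design effect = 1 + (400 − 1) × 0.01 = 4.99
- Effective size per group = 2,800 / 4.99 = 561
- Standard error = √(2 × 0.725 × 0.275 / 561) = 0.0267, or 2.67 points

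**2. The protocol's own power figure**
- Women per group before clustering = (1.960 + 1.645)² × 2 × 0.725 × 0.275 / 0.10² ≈ 519
- After clustering = 519 × 4.99 ≈ 2,590, which is 2,590 / 400 ≈ 6.5 practices, rounded up to 7
- Power at 2,800 per group = Φ(0.10 / 0.02666 − 1.96) = 96.3%; with a t distribution on 12 degrees of freedom (14 practices − 2), 93.0%

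The stated 95% reproduces, so the trial is adequately sized for a 10-point margin. A relative margin (0.10 × 72.5 = 7.25 points) would give only Φ(0.0725 / 0.02666 − 1.96) = 78%, so the absolute reading is the one that fits.

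**3. Largest observed loss that still passes**
- Normal: −10 + 1.96 × 2.67 = −4.8 points
- t, 12 df: −10 + 2.179 × 2.67 = −4.2 points

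**4. Chance of meeting the primary criterion, by true loss**

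P(pass) = Φ((0.10 − loss) / SE − 1.96), with SE recalculated at the reduced rate. For a 5-point loss, SE = √((0.675 × 0.325 + 0.725 × 0.275) / 561) = 0.0273, so P = Φ(0.05 / 0.0273 − 1.96) = 45%.

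| True loss (points) | Normal | t, 12 df |
|---|---|---|
| 0 | 96% | 93% |
| 2 | 84% | 78% |
| 3 | 73% | 66% |
| 5 | 45% | 39% |
| 7.5 | 15% | 13% |
| 10 | 2.5% | 2.5% |

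**5. The follow-on comparison with zero**
- If coverage is truly equal, the lower limit exceeds zero 2.5% of the time.
- 80% power for a lower limit above zero needs a true gain of about 7.2 points (7.8 with t).
- At true equality, the planning assumption, non-inferiority alone is therefore the result in about 96.3 − 2.5 = 94% of trials (93.0 − 2.5 = 90.5% with t).

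**6. The margin against the protocol's target**
- Table 1: 80 − 74.0 = 6.0 points short of target
- Sample size section: 80 − 72.5 = 7.5 points short of target

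Both shortfalls are smaller than the value described as the smallest that is clinically relevant.

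**The case against.** The operative text is clear enough on its own. The primary aim is worded as non-inferiority, the Sample size section spells out what the margin means, and the Data analysis section fixes the limit and keeps the test at -10 separate from the test at zero. The hypothesis can be read as the investigators' expectation, consistent with planning on equal rates, and the Overview wording is an aspiration. The pass probabilities are simply how a 10-point margin behaves at this precision. A margin might also be defended because the new test is the more effective one.

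Much of this stands. The rule is not ambiguous, the probabilities show no fault in the design, and the zero comparison is a real partial safeguard. It does not remove the conflict: the adoption condition says what must be proven and equates it with non-inferiority, while the step that could support it is conditional and is not what the trial was sized for. Nor does the protocol offer the effectiveness of the test as its reason for the margin.

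Three stronger readings are tempting but unsupported.

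- A reader might infer that a pass will be reported as no loss of coverage. The protocol fixes no reporting wording, and its Sample size section states the margin correctly.
- A reader might set the margin against the gap in Table 1 between Māori and European/Other women (78.9 − 66.2 = 12.7 points). That gap exceeds 10, so it contradicts nothing.
- A reader might turn the margin into a regional headcount and compare it with the extra screens needed to reach target. That carries a margin tested over one year across to three-year coverage ending in March 2016, an assumption the documents do not support.

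**Conclusion.** The mismatch is real and lies in the current text. A pass on the primary criterion shows that coverage is less than 10 points lower; it does not show that it is at least equal, which is what the adoption condition asks for. At the planned precision the rule admits an observed loss of 4.2 to 4.8 points, and it passes a true 5-point loss 39 to 45% of the time and a true 3-point loss 66 to 73% of the time. These figures assume the planned 72.5%, equal practices of 400 women and an intra-cluster correlation of 0.01; the ranges run from t on 12 degrees of freedom to the normal approximation.

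The sample size is sound for the stated margin, and the point is not that 10 points is unusable. The rationale for it, however, is a bare assertion that sits uneasily with a total shortfall to target of 6.0 to 7.5 points. Distance to a target is not the same quantity as a smallest relevant difference between groups, so this is a reason to ask for a justification and does not prove the margin wrong. The correction is worth making because it bounds what the trial may conclude.

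**What to change.** Keep the -10 margin and change the wording around it.

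- **Universal offer of HPV self-testing:** delete the parenthesis that explains non-inferior as equal, and state the condition as coverage not more than 10 percentage points lower than under the present programme.
- **Aim:** state the primary hypothesis in the same terms.
- **Data analysis:** add that coverage at least equal to the present programme, or no loss of coverage, may be concluded only if the lower 95% limit is at or above zero, using the follow-on comparison already described.
- **Sample size:** justify the sentence calling the margin the smallest clinically relevant value, or delete it.

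This needs a protocol wording amendment only, with no change to sample size or analysis. The cost is a less favourable headline if only non-inferiority is met, which is the most likely result if coverage is truly equal.
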